**Outcomes**								
Main coronal Cobb angle	X			X	X	X	X	X
Serious Adverse Events			X	X	X	X	X	X
Implant length				X	X	X	X	X
EOSQ-24 questionnaire	X			X	X	X	X	X

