### Outcomes

The primary outcomes include coronal Cobb angle – measured on radiographs – and occurrence of SAEs (defined as unplanned medical events which (could) result in permanent disability/damage, or which requires (lengthening of) hospitalization, a re-operation, or inpatient medical managing). SAEs will be categorized as either device/surgery related (e.g. rod fracture, post-operative neurological deficit), or as disease-related (e.g. pneumonia, pain) according to a previously created complication classification system for use in EOS treatment [24]. In addition to SAEs, complications that do not meet the criteria for an SAE, but which are device/surgery related (e.g. superficial infections, proximal junctional kyphosis) will also be recorded.

Secondary radiographic measurements include parameters such as T1-T12, T1-S1 and instrumented height, T5-T12 kyphosis, L1-S1 lordosis, and pelvic obliquity. In addition, implant length will be calculated at each timepoint for both groups (SDS: Spring length, OWSER: Notched rod length) so that implant growth velocity over time can be graphed and calculated. The number of outpatient axial traction events of OWSER patients, if these are performed, will also be reported. All radiographic measurements will be performed by a trained assessor. To ensure data quality, radiographic measurements are performed semi-automatically in Surgimap v2.3.2.1 software (Nemaris, New York, USA), after which all measurements are audited by the assessor. At the end of the data collection phase, all radiographic measurements are re-assessed by a second trained assessor who is blinded to the first assessors’ measurements. Measurements are compared and disputed measurements are discussed until consensus is reached. If differences are believed to be caused by random measurement variation, the arithmetic mean of both assessors’ measurement is taken.

HRQoL will be measured with the validated Dutch version of the EOSQ-24 which consists of 24 questions in 10 domains, from which a domain- and total score is calculated [25, 26]. All outcome parameters are measured pre-operatively, immediately post-operatively, and at 1, 3, 6, and 12 months follow-up.

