### Sample size calculation and statistical methods

The sample size calculation is based on potential differences between groups in maintenance of the coronal curve between the post-operative situation and 1-year follow-up. A difference in Cobb angle ≥ 5˚ is considered clinically relevant and can be reliably measured [27]. In our previous MCGR cohort studies, we found a change in Cobb angle between post-operatively and 1 year follow-up of 1˚ (SD 5.1˚) [28]. To determine differences in curve maintenance between groups ≥ 5˚ with a power (1-β) of 0.8, α = 0.05, and SD = 5.1˚, we calculated a sample size of n = 28, with a repeated measures ANOVA between factors design (comparing 2 timepoints). With an allocation ratio of 1:1, this means that 14 patients have to be included in each experimental group.

If all assumptions for performing repeated measures ANOVA are met, both systems will be compared with respect to coronal curve maintenance; age and sex will be included as covariates. For the other continuous variables, repeated measures ANOVA will be used, with the same covariates, but including all evaluated time points. If the assumptions for performing repeated measures ANOVA are not met (e.g. due to missing data), repeated measurement multilevel modelling will instead be performed, with patient, age, sex and treatment group as level 2 variables, and follow-up time as a level 1 variable.

A Kaplan–Meier survival analysis will be performed comparing both groups. The survival curves showing SAE-free survival of both groups will be statistically compared with the Log-Rank test. Analysis of EOSQ-24 scores will be performed using repeated measures ANOVA. In case there are missing EOSQ-24 item scores or questionnaires, multiple imputation with parcel summary scores will be performed using a previously published statistical method [29]. For all statistical tests, statistical significance will be set at *p* < 0.05. All statistical analyses will be performed in IBM SPSS statistics v.26.0.0.1 (Chicago, USA).

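### The pre-allocation EOSQ-24 score enters the repeated measures ANOVA as an outcome visit and not as a covariate, which loses a substantial part of the power of the secondary quality-of-life comparison

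*Protocol article*

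**What the plan says.** All of this is in the Protocol article.

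- **Analysis of the questionnaire** (Sample size calculation and statistical methods): "Analysis of EOSQ-24 scores will be performed using repeated measures ANOVA". The sentence names neither visits nor covariates.
- **Visits and covariates in the model** (same section): for continuous variables other than coronal curve maintenance, the ANOVA takes in every time point evaluated and uses the same covariates, age and sex. The multilevel fallback, used if the ANOVA assumptions fail, lists patient, age, sex, treatment group and follow-up time. Neither model has a pre-operative score as covariate.
- **Measurement times** (Outcomes): "All outcome parameters are measured pre-operatively, immediately post-operatively, and at 1, 3, 6, and 12 months follow-up". That is one pre-operative and five post-operative scores.
- **Order of events** (Table 1; Randomization and blinding): the row "EOSQ-24 questionnaire" is marked at enrolment, earlier than two weeks before surgery, and is blank at allocation. The allocation envelope is retrieved two weeks before surgery.
- **Role** (Study aims): describing and comparing quality of life is a secondary aim. No power, SD, correlation or target difference is stated for it.

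**The concern.** A score taken before allocation carries no treatment effect, but it does carry information on how each child will score later. In the stated model it works the wrong way round. Averaged into the group main effect, it adds a visit where the true difference is zero, and the lasting differences between children stay in the error term. Used through the group-by-time interaction, it does remove those differences, but the test is spread over 5 degrees of freedom. The section does not say which of the two terms is the comparison.

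Eligibility covers any neuromuscular or syndromic EOS in non-ambulant children under 12, so starting scores are likely to differ widely. The trial has 28 children and was sized on Cobb angle. A real difference in quality of life could be missed although the data to show it more clearly are already being collected.

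**Working it through.** **The plan's own figure.** The sample size rests on a 5° difference "with a power (1-β) of 0.8, α = 0.05, and SD = 5.1"°, and the protocol states: "we calculated a sample size of n = 28, with a repeated measures ANOVA between factors design (comparing 2 timepoints"). For the between-factors test, f = (5/5.1)/2 = 0.490 and λ = N·f²·2/(1+ρ). With ρ = 0.5 (assumed; not stated) and N = 28, λ = 28 × 0.2403 × 2/1.5 = 8.97 and power is 0.822; N = 26 gives 0.791. So 28 reproduces. It concerns the Cobb angle and says nothing about the EOSQ-24.

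**Inputs for the EOSQ-24**
- From the protocol: 14 per arm (N = 28), six visits of which five are post-operative, covariates age and sex. "For all statistical tests, statistical significance will be set at" p < 0.05, taken here as two-sided.
- Assumed: compound symmetry with equal variances, correlation ρ between any two visits, no difference before surgery, and a constant difference d = 0.8 SD at all five post-operative visits.

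**Noncentrality** (factor N/4 = 7)
- Main effect over six visits: effect 5d/6, variance (1+5ρ)/6; 1 and 24 df.
- Group-by-time: the profile (0, d, d, d, d, d) has sum of squares about its mean of (25/36 + 5/36)d² = (5/6)d², so λ = 7·(5/6)d²/(1−ρ); 5 and 120 df.
- Mean of the five post-operative visits adjusted for the pre-operative score: effect d, variance (1+4ρ)/5 − ρ²; 1 and 23 df.
- 12-month score alone, adjusted in the same way: effect d, variance 1 − ρ²; 1 and 23 df.

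**Worked at ρ = 0.5**
- Main effect: 7 × 0.6667²/0.5833 = 5.33, power 0.60.
- Interaction: 7 × 0.5333/0.5 = 7.47, power 0.51.
- Adjusted mean: 7 × 0.64/0.35 = 12.8, power 0.93.

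Here 5.33 + 7.47 = 12.8. Under these assumptions the adjusted analysis collects on one degree of freedom the information that the ANOVA splits between two tests.

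| ρ | Main effect | Interaction | Adjusted post-operative mean | Adjusted 12-month score |
|---|---|---|---|---|
| 0.4 | 0.67 | 0.43 | 0.92 | 0.60 |
| 0.5 | 0.60 | 0.51 | 0.93 | 0.65 |
| 0.6 | 0.55 | 0.62 | 0.95 | 0.72 |
| 0.7 | 0.50 | 0.76 | 0.97 | 0.81 |

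**Varying the assumptions**
- *Effect set so that the adjusted mean has 80% power, ρ from 0.3 to 0.8:* the main effect has 57% falling to 21%, and the interaction 25% rising to 49%.
- *Weaker link across surgery (ρ = 0.6 between post-operative visits, 0.3 from pre- to post-operative, d = 0.8):* the adjusted variance is 0.68 − 0.09 = 0.59, so λ = 4.48/0.59 = 7.59 and power is 0.75. The main-effect variance is (6 + 2(10 × 0.6 + 5 × 0.3))/36 = 0.583, giving power 0.60.
- *Difference growing linearly to 12 months, set so that the adjusted 12-month test has 80% power, ρ from 0.3 to 0.8:* interaction 57% to 73%, main effect 25% down to 9%, adjusted post-operative mean 38% down to 28%.

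**The case against.** The strongest reply is that the plan is valid. Under randomisation the ANOVA does not bias the group comparison. Quality of life is a secondary aim with no power claimed, the discussion treats the results as an initial indication only, and keeping the pre-operative visit shows change after surgery. All of that stands. It makes this a matter of efficiency and not of error.

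The reply can also say that the EOSQ-24 sentence by itself does not put six visits in the model. That is correct: the point needs the sentence on the other continuous variables and the visit list. If that sentence governs the EOSQ-24, age and sex are covariates; if it does not, none is named. The pre-operative score is a covariate on neither reading, so the point survives both.

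The size rests on assumptions that the documents cannot confirm. A weak pre-to-post correlation shrinks the gain. If the difference builds up towards 12 months, the planned interaction test loses less against an adjusted 12-month test, and it beats the adjusted average over all post-operative visits. The adjusted average is better than the planned main effect in every case computed, but it is not better than the interaction for every effect shape.

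A reader might infer that most of the power is thrown away. The figures do not support that in general. At ρ = 0.5 the planned tests keep 0.60/0.93 = 65% and 0.51/0.93 = 55% of the adjusted power; at ρ = 0.7 the interaction keeps 0.76/0.97 = 78%.

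**Conclusion.** The point holds as a loss of efficiency in a stated method. The protocol fixes the model and the covariates, uses a clean pre-allocation score as an outcome level, and adjusts for it in neither the ANOVA nor the fallback. For a constant post-operative difference of 0.8 SD, power is 0.50 to 0.67 (main effect) or 0.43 to 0.76 (interaction), against 0.92 to 0.97 with adjustment, for correlations of 0.4 to 0.7. These figures assume compound symmetry, and the correlation and the effect size are assumptions as well.

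The loss is substantial but cannot be put at a single figure, because the tested term, the correlation and the course of the difference over time are all unstated. Nothing here shows bias, and nothing touches the Cobb-angle sample size. For a secondary outcome this is a change that should be made, not a condition for the trial to be sound.

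**What to change.** In the repeated measures ANOVA, and in the multilevel model if the fallback is used:

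1. Take only the five post-operative EOSQ-24 scores as outcomes.
2. Add the child's pre-operative score as a covariate, with age and sex.
3. Name the SDS minus OWSER difference averaged over the post-operative visits as the comparison, with its confidence interval.
4. Give the 12-month difference from the same model as a supporting estimate. Its power is about 0.60 to 0.81 under the table's assumptions, and it is the more informative contrast if the difference builds up late.
5. Report change from the pre-operative score descriptively.

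The choice of comparison should be fixed before outcome data are compared by group. The cost is one degree of freedom and a change of wording; no new data, visits or patients are needed.

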## Discussion

Current treatment of EOS is largely based on opinion and physician’s experience. This low level of evidence has many reasons, which start with the broad definition of EOS. Currently, any scoliosis that initiated before age 10 is regarded as EOS. Since many curves only become problematic during the growth spurt, these can often be treated through spinal fusion and do not require “growth-friendly” surgery. Patients that may be eligible for “growth-friendly” surgery likely had a curve onset much earlier and therefore are a distinct subgroup. Another issue is that most data comes from combined registries which include patients with heterogeneous etiologies (varying from severely disabled children to completely heathy), surgical indications and implant types. In addition, most treatment strategies are just being discovered and promising techniques such as MCGR appear much more vulnerable to failure than expected [12]. Therefore, long-term follow-up of large groups is simply absent. Finally, if results are reported, these studies are often inconsistent, incomparable, and of poor methodological quality, as reflected in a previous systematic review [30].

To investigate “growth-friendly” implants or strategies that are typically used in small numbers, we believe a prospective study on a specific population with a specific technique is essential, preferably with follow-up until after final fusion. Such a design demands a lot of effort, even before including patients, starting with a rigorous protocol, installation of a dedicated research team and IRB approval. The BiPOWR trial is the first surgical randomized trial to be performed in children with EOS, designed to investigate the limited-efficacy and safety of two novel “growth-friendly” systems.

Although the study will generate high level evidence, there are several limitations to consider. First, this study does not investigate if growth friendly surgery is actually better than continuing conservative treatment, as we only compare surgical treatments. Also, this study does not have a control group, as we compare the SDS with the OWSER, instead of a ‘gold standard’ surgical treatment – i.e., TGRs and/or MCGRs. We chose this design deliberately as we experienced many problems with current standard therapies, from which we conclude that there simply is no accepted ‘gold standard’. In fact, many of our patients are referred to our center because we have the possibility to offer these novel treatments. It would be unethical to ask these patients to be randomized to a treatment of which we know it has serious disadvantages. Obviously, the patient can always choose not to be included in the study and opt for conventional treatments such as TGR or MCGR that we perform regularly.

Second, the primary endpoint is at only one year follow-up. It is possible and likely that complications manifest after this period as is also seen with conventional “growth-friendly” systems [11, 12, 31]. The primary endpoint is, in that sense, a short-term interim analysis to look at early mechanical failures and short-term efficacy, hence the limited-efficacy nature of the study. After completion of the 1-year analysis, both cohorts of patients will be followed for several years until (and even after) skeletal maturity. Only at that point, definitive conclusions regarding efficacy can be drawn. For practical reasons, we did not incorporate the long-term analysis into the primary aim of the BiPOWR trial.

Third, although randomization is obviously a strong method to minimize bias in comparative studies, this carries the risk of being too artificial and not representative [32–34]. One way to mitigate this, is a multicenter approach and sufficient learning curve for both treatments. We recognize, however, that the investigated techniques are new, and only practiced by a selective group of surgeons. This means that the outcomes of the BiPOWR trial should only be used as an initial indication of efficacy and safety. These findings should be confirmed with larger observational studies and registry data.

## Data Availability

Access to BiPOWR study data is limited to the research team, study monitors, and the DSMB. However, the full protocol, participant-level dataset, and statistical code are available upon reasonable request after consultation with the principal investigator.

## Abbreviations

ANOVA: Analysis of Variance
BiPOWR: Bilateral Posterior One-Way Rod
CCMO: Central Committee on Research Involving Human Subjects
CE: Conformité Européenne
CoCr: Cobalt-Chromium
EOS: Early Onset Scoliosis
EOSQ-24: Early Onset Scoliosis Questionnaire
HRQoL: Health-Related Quality of Life
MCGR: Magnetically Controlled Growing Rod
OWSER: One Way Self-Expanding Rod
SAE: Serious Adverse Event
SD: Standard Deviation
SDS: Spring Distraction System
TGR: Traditional Growing Rod
Ti6Al4V: ASTM Grade 5 titanium (medical grade)
